**Primary outcome—individual**						
LS7 cardiovascular health score (0–14)	Composite [103, 104]		X	X	X	X
**Secondary outcomes—individual**						
BMI^a^	Self-measured		X	X	X	X
Waist circumference (in)	Self-measured		X	X	X	X
High/elevated blood pressure (y/n)^a^	Classified from self-reported measurements, diagnosis, and medication use		X	X	X	X
High/borderline total cholesterol (y/n)^a^	Classified from self-reported measurements, diagnosis, and medication use		X	X	X	X
Diabetes/pre-diabetes (y/n)^a^	Classified from self-reported measurements, diagnosis, and medication use		X	X	X	X
General health status	SF-36 general health item [105]		X	X	X	X
Current smoker (y/n)^a^	LS7 item [103, 104]		X	X	X	X
Total HEI score (1–100)	Single 24-h recall collected via the ASA24 [95]		X	X	X	X
Total fruit and vegetable intake (cups/day)^a^	LS7 item [103, 104]; ASA24 [95]		X	X	X	X
Consumption of whole grains (servings/day)^a^	LS7 item [103, 104]; ASA24 [95]		X	X	X	X
Fiber intake (g/day)	DSQ [106, 107]; ASA24 [95]		X	X	X	X
Met recommendation for fish consumption (y/n)^a^	LS7 item [103, 104]		X	X	X	X
Consumption of ultra-processed foods (% total kcal)	ASA24 [95]		X	X	X	X
Frequency of consuming ultra-processed foods (times/month)	Adapted from DSQ [106] and BSQ2 (9 items) [108]; ASA24 [95]		X	X	X	X
Red and processed meat consumption (g/week)	Estimated from DSQ [106, 109]; ASA24 [95]		X	X	X	X
Alcohol consumption (drinks/day)	Adapted from the AUDIT (2 items) [110]; ASA24 [95]		X	X	X	X
Total steps per day	Average of self-reported pedometer or wearable fitness tracker readings		X	X	X	X
Total physical activity (MET-min/week)^a^	IPAQ-long [111]		X	X	X	X
World Cancer Research Fund/American Institute for Cancer Research recommendation adherence score (0–7)	Composite [112]		X	X	X	X
Healthy eating motivation (1–5)	Adapted Naughton & McCarthy Healthy Eating Motivation Scale (3-items) [113]		X	X	X	X
Confidence for healthy eating (1–5)	Adapted from Sallis Eating Habits Confidence Survey and Seguin-Fowler Expanded Eating Habits Confidence Survey (7-item) [114, 115]		X	X	X	X
Social support for healthy eating (1–5)	Ball Social Support for Healthy Eating Scale [116]		X	X	X	X
Exercise attitudes (1–5)	Adapted from Sect. 2, question 5 of the AARP Exercise Attitudes and Behaviors Survey (4 items) [117]		X	X	X	X
Exercise confidence (1–5)	Adapted from Sallis Exercise Confidence Survey (3 items) [115]		X	X	X	X
Social support for physical activity (1–5)	Ball Social Support for Physical Activity Scale [116]		X	X	X	X
**Secondary outcomes—collective**						
Social engagement (family and friends) (1–5)	Lubben Social Network Scale [118]		X	X	X	X
(Community) social cohesion (1–5)	Social cohesion sub-scale of the Mujahid et al. NES [119]		X	X	X	X
Individual mobilization (1–5)	Human capital sub-scale of the Jakes & Shannon Mobilization Scale – Individual [120]		X	X	X	X
General civic engagement attitudes (1–5)	Attitudes sub-scales of the Doolittle & Faul Civic Engagement Scale [121]		X	X	X	X
General civic engagement behaviors (1–5)	Behaviors sub-scale of the Doolittle & Faul Civic Engagement Scale [121]		X	X	X	X
Investment in community health (number of priorities) (0–5)	Investment in community health sub-scale of the RWJF National Survey of Health Attitudes [122]		X	X	X	X
**Secondary outcomes—environment**						
Walking environment (1–5)	Adapted walking sub-scale of the NES (7 items) [119]		X	X	X	X
Neighborhood safety (1–5)	Adapted neighborhood safety sub-scale of the NES (3 items) [119]		X	X	X	X
Neighborhood aesthetic (1–5)	Adapted neighborhood aesthetic sub-scale of the NES (2 items) [119]		X	X	X	X
Fresh FV availability (1–5)	Adapted from fresh fruit and vegetable availability sub-scale of the Green & Glanz NEMS-P (3 items) [123]		X	X	X	X
Store selection motivation (1–5)	Adapted from the store selection motivation sub-scale of NEMS-P (3 items) [123]		X	X	X	X
Restaurant healthy food availability (1–5)	Adapted from the restaurant healthy food availability sub-scale of NEMS-P (2 items) [123]		X	X	X	X

^a^Simple 7 components

*ASA24* Automated Self-Administered 24-Hour Dietary Assessment, *AUDIT* Alcohol Use Disorders Screening Test, *BMI* body mass index, *BSQ* Beverage and Snack Questionnaire, *DSQ* NHANES Dietary Screener Questionnaire, *HEI* Healthy Eating Index, *IPAQ-long* International Physical Activity Questionnaire long form, *LS7* American Heart Association’s Life’s Simple 7, *SF-36* 36-Item Short Form Survey, *NEMS-P* Perceived Nutrition Environment Measures Survey, *NES* Neighborhood Environment Scale, *RWJF* Robert Wood Johnson Foundation

### Process evaluation

The process evaluation is designed to understand implementation of both the diet and PA content and the civic engagement aspect of the intervention. We will assess implementation outcomes (see Table 5): dose received (acceptability and appropriateness of the intervention, how participants experienced the intervention, attendance, satisfaction, cultural compatibility/relevance); fidelity (to what degree the intervention was implemented as intended, what was adapted and how); feasibility (perceptions on how feasible it was to integrate the intervention into usual activities); and group functioning (functional and dysfunctional group dynamics, satisfaction with the group) [124]. Using the Consolidated Framework for Implementation Research (CFIR) [125], we will also collect data related to barriers and facilitators to implementation that could impact future uptake of the intervention. The CFIR has 26 constructs within five major domains: intervention, inner and outer settings, individuals involved, and process by which implementation is accomplished. The study team has pre-selected the constructs most relevant to implementation of both the nutrition and PA content and civic engagement component and are the most likely to vary across community sites. Lastly, process evaluation data will help elucidate CC action plan outcomes (goal achievement and impact) as well as the mechanisms by which any individual-level outcomes are realized among CCM, friends and family members, and community residents. Data will be collected using both surveys and qualitative in-depth interviews. More details about the process evaluation data collection instruments and their purpose and time schedule are presented in Table 5.

**Table 5 Tab5:** Process evaluation assessment plan and timeline

INSTRUMENT	DATA COLLECTED	PARTICIPANT CATEGORY	TIMEPOINT(S)	COMPENSATION	NOTES
Post-Meeting Surveys	-Implementation outcomes, nutrition and PA content (*dose received*: attendance, perceived participant satisfaction, engagement, appropriateness/fit, relevance/usefulness; *fidelity*: components covered, to what degree, enhancements/modifications, meeting start & end times; *feasibility*: prep time, cost)	Facilitators/ Educators	After each meeting	N/A	CC cost questions asked on final Post-Meeting Survey
Post-Theme Surveys	-Implementation outcomes, nutrition & PA content (dose received) -Implementation outcomes, CC action plan (group functioning) -Mechanisms of outcomes (perceptions about personal behavior change)	CCM^a^	After each curriculum theme^b^	$20^c^	Participant cost questions asked on first Post-Theme Survey only
Post-Curriculum Interview Guide	-Barriers and facilitators to implementation of nutrition and PA content (CFIR constructs)	Educators	At conclusion of all curriculum modules	N/A	
Post-Curriculum Interview Guide	-Implementation outcomes, nutrition & PA content (dose received) -Implementation outcomes, CC action plan (group functioning) -Mechanisms of outcomes (perceptions about personal behavior change; perceptions about how CC action plan will impact community)	CCM^d^	At conclusion of all curriculum modules	$40	
Check-In Survey	-Implementation outcomes of the CC action plan (fidelity to action plan, group functioning) -CC action plan outcomes (goal achievement, impact)	Educators	Monthly for 12 months, starting one month after conclusion of all curriculum modules	N/A	CC cost questions asked on final Check-In Survey
One Year Post Interview Guide	-Barriers and facilitators to implementation of the CC action plans (CFIR constructs) -CC action plan implementation outcomes (fidelity, group functioning) -CC action plan outcomes (goal achievement, impact) -Mechanisms of outcomes (CCM only: perceptions about personal behavior change)	Educators, CCM	12 months after the conclusion of all curriculum modules	$40 (CCM only)	
Mini-Interview Guide	-CC action plan outcomes (perceptions of impact on community) -Mechanisms of community resident outcomes (perceptions of impact on self)	Community Residents^e^	12 months after the conclusion of all curriculum modules	$20	
Online Survey: Process Evaluation Questions	-CC action plan outcomes (current activities, goal achievement, new initiatives)	CCM	12-, 24-, and 36-month timepoints	Part of overall study compensation	Process evaluation questions will be included in the annual online survey
Online Survey: Process Evaluation Questions	-Mechanisms of friends and family members, community resident outcomes (awareness of CC project^a^; involvement in CC project^a^; involvement in any other community change initiatives; awareness of changes in behavior or weight loss of community members)	Friends and Family Members, Community Residents	12-, 24-, and 36-month timepoints	Part of overall study compensation	Process evaluation questions will be included in the annual online survey
Two Year Post Interview Guide	-CC action plan outcomes (goal achievement, new initiatives) -Implementation outcomes (sustainability)	Educators	24 months after the conclusion of all curriculum modules	N/A	Will include CC cost questions

^a^ Only those in intervention community

^b^ Or at other appropriate intervals, depending on meeting structure

^c^ Must complete all surveys to receive compensation

^d^ Random sub-sample from each CC

^e^ Approximately 15 per intervention community

*CC* Change Club, *CCM* Change Club Members, *CFIR* Consolidated Framework for Implementation Research, *PA* Physical Activity

Qualitative interviews will be analyzed using a directed qualitative content analysis approach [126–128] in a two-step process: an initial codebook will be drafted based upon the questioning structure; transcripts will then be reviewed, and codes added for topics that arise consistent with the formative evaluation goals. The NVivo program (QSR International) will be used to assist with data analysis. Transcripts will be coded so that comparisons can be made across communities. Once the coding scheme is finalized, a sample of 10% of randomly chosen transcripts will be coded by two team members to estimate inter-rater reliability [126]. Code definitions will be refined until high inter-rater reliability is achieved. The remaining transcripts will be coded using this final codebook with systematic checks for fidelity. Coded text will then be summarized by team members to highlight key themes and sub-themes. We will use these codes to identify themes by location, key distinctions in experiences, relationships with quantitative data, and important non-conforming cases.

### Cost analysis

Cost analysis will include a program and site-specific cost analysis as well as an exploratory cost-effectiveness analysis on LS7 (and secondary outcomes as appropriate) from the payer perspective, which means we will estimate how much the intervention’s payer or sponsor paid for the intervention, focusing on costs directly incurred to administer and implement the program. We will collect data on the costs of the resources used in CC interventions at approximately 6-, 18-, and 30-months post-CC initiation. The costs incurred by CCM, such as travel and equipment in order to participate, will be based on costs spent to attend the first meeting. Collection of cost data will be integrated into the process evaluation surveys of CCM and facilitators. Costs will include wages for CC facilitator time and rented meeting space. Other costs will vary across the menu of CC interventions (e.g., resources used in media and educational campaigns, trail signage). Total costs for each CC will be summed and compared with CC impact estimates in each community.

### Social network analysis

We will use egocentric social network analysis to assess outcomes among CCMs and their friends and family, and whether social network properties, including composition and structure, are associated with outcomes among participants. Egocentric networks will be identified using the unique link each CCM uses to invite their friends and family to participate, and name interpreter and inter-relater questions will be included in the surveys completed by CCMs and their friends and family members [129]. CCM members will then answer name interpreter questions about their friends and family members including how often they see each friend or family member and the support they receive from each friend or family member. Friends and family members also will respond to identical questions about the CCM. Compositional and structural variables will be calculated using E-NET statistical software [130], and analyses will be completed using R statistical language software [131].

### Statistical analysis

#### Sample size determination

Our sample size targets are based upon the ability to detect significant difference between arms at the 24-month post-baseline time period using a t-test, with a desired power of 80%, an alpha level of 0.05, and a two-sided test. The sample size requirements for this study are based on our prior intervention studies [132, 133], which were six months in length and demonstrated an effect size of + 0.7–0.8 units in the LS7 composite score. We aim to recruit 70 CCM in intervention and 70 in control and, based on our prior CC work [133], we estimate 10% attrition each year, resulting in 57 CCM in each arm at 24-month follow-up. Cluster sizes were assumed to be consistent across communities, and the intraclass correlation of participants within those clusters is estimated to be 0.025. This adjustment results in an effective sample size of 45 CCM per arm and an ability to detect an effect size of 0.60 SDs (approximately 1 unit in the LS7 composite score).

We will enroll 560 friends and family members in intervention communities and 560 in control communities but anticipate greater attrition (20% per year) and larger clustering of friends and family members around CCM and within communities (ICC = 0.08). The effective sample size will be 252 friends and family members per arm at 24-month follow-up, and an ability to detect an effect size of 0.25 (approximately 0.4 change in LS7 composite score).

We also will enroll 400–500 community residents in intervention communities and 400–500 in control communities. We estimate 20% attrition per year among community residents and an ICC of 0.025, resulting in an ability to detect an effect size of 0.36 (mid-way between the effect sizes detectable in CCM and friends and family members samples).

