### Communities

The study will be carried out in ten paired communities in two states (four in New York and six in Texas). These communities are rural per the Rural–Urban Commuting Area version 2.0 definition [20, 82] and are designated as medically underserved areas and/or Health Professional Shortage Areas [83]. Randomization (based on random numbers computer-generated by research staff) will occur after baseline measurements are collected in both communities within a pair, with five communities starting the CC process and resident-led implementation activities directly after randomization and the remaining five communities serving as controls. It is not feasible to conceal assignment to intervention or control from participants or research staff due to the nature of the design; however, field staff involved in intervention delivery will not be involved in assessing outcomes. At the conclusion of data collection (36 months after baseline), the five control communities will be provided with intervention materials, but their outcomes will not be measured after that time point.

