#### Outcome analysis

All continuous variables will be examined for normality and, if not met, outliers will be investigated and rectified, and variables will be transformed to improve the distributions or non-parametric tests will be used [134]. Univariate descriptive statistics for all variables will be examined for all sample members pooled. Missing data will be examined for missingness at random and imputed using hierarchical multiple imputation methods [135–137]. Baseline outcome measures will be summarized with means and standard deviations for each treatment arm separately. Comparisons across arms will be completed using Chi-square tests (binary and categorical variables), t-tests (continuous variables), or non-parametric tests when warranted. Change from baseline will be calculated for each outcome variable at each point in time. Change at 36 months relative to 24 months also will be calculated to examine behavior maintenance.

Mixed models will test for differences in change in outcomes 24 months post-baseline between intervention and control arms by modeling a change score with control for baseline value and including community as a random effect to reflect clustering of persons within community (the level at which random assignment will occur). For dichotomous outcomes (e.g., current smoker, met whole grain recommendation), variables will be analyzed as assessed at 24 months post baseline with control for baseline value, and community as random effect. Secondary endpoints analysis will be conducted similarly to test for 12-month and 36-month change from baseline in intervention relative to control, as well as 36-month change from 24-month to test for maintenance of any observed 24-month effects. All tests will be considered significant at p < 0.05 with two-tailed tests.

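### The three detectable effects come from an individual-level t-test on an effective n, but ten randomised communities leave 8 degrees of freedom, so power at those effects is about 66–70%, not 80%

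*Protocol article*

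**What the plan says.** Under Sample size determination, detectable effects are set for a comparison "at the 24-month post-baseline time period using a t-test, with a desired power of 80%, an alpha level of 0.05, and a two-sided test". Enrolment starts from "We aim to recruit 70 CCM in intervention and 70 in control". With 10% attrition per year, 57 CCM per arm are expected at 24 months, and an ICC of 0.025 is applied: "This adjustment results in an effective sample size of 45 CCM per arm", with 0.60 SD detectable, given as roughly 1 LS7 unit. Friends and family (560 per arm, 20% attrition per year, ICC 0.08) are given an effective n of 252 per arm and 0.25 SD. Community residents (400–500 per arm, 20% attrition per year, ICC 0.025) are given 0.36 SD.

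Under Communities, the units randomised are "ten paired communities in two states (four in New York and six in Texas"), "with five communities starting the CC process and resident-led implementation activities directly after randomization and the remaining five communities serving as controls". Under Outcome analysis, the 24-month comparison is a mixed model of the change score, adjusted for baseline and "including community as a random effect to reflect clustering of persons within community". That section identifies community as the unit of random assignment. No method for the degrees of freedom is named.

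**The concern.** A design effect corrects the variance of the arm difference for clustering. It does not correct the degrees of freedom with which that variance is estimated. Those come from the number of randomised units, here five communities per arm. A t-test on 45 effective people per arm uses 88 df and a critical value of 1.99. With 8 df the critical value is 2.31.

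If the stated effects were computed on the larger df, the article claims 80% power at differences where the design offers less. The CCM margin is already thin: the article cites earlier effects of 0.7–0.8 LS7 units, while its detectable 0.60 SD is about 1 unit. The same small number of communities also bears on how the mixed-model test is carried out.

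**Working it through.** **Inputs.** All are from Sample size determination, except the five communities per arm, which are from Communities.

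**Formulas.** Effective n per arm = retained n / [1 + (m − 1) × ICC], with m the retained cluster size. Non-centrality = d × √(effective n / 2). Power = P(noncentral t > critical value), two-sided alpha 0.05. The non-centrality is the same whichever df are used; only the df change.

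**Step 1: reproduce the article's figures (df = 2 × effective n − 2).**
- *CCM.* 70 × 0.9² = 56.7, stated as 57. m = 57/5 = 11.4; design effect 1 + 10.4 × 0.025 = 1.26; 57/1.26 = 45.2, stated as 45. With 88 df the effect detectable at 80% power is 0.597 SD (stated 0.60).
- *Friends and family.* 560 × 0.8² = 358.4. The stated 252 is recovered by taking the 57 retained CCM per arm as clusters: m = 358.4/57 = 6.29; design effect 1 + 5.29 × 0.08 = 1.423; 358.4/1.423 = 251.9. With 502 df the detectable effect is 0.250 SD (stated 0.25).
- *Residents.* 400–500 × 0.8² = 256–320; m = 51.2–64; design effect 2.255–2.575; effective n 113.5–124.3. With about 225–247 df the detectable effect is 0.373–0.357 SD (stated 0.36). Power at 0.36 SD is 77% with 400 per arm and 81% with 500.

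All three stated effects are therefore recovered with individual-level df.

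**Step 2: repeat with df = 10 − 2 = 8.** The critical value is 2.306, and the non-centrality needed for 80% power rises from 2.81–2.83 to 3.20.

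| Sample | Effective n per arm | Stated effect (SD) | Power, plan's method | Power, 8 df | Effect at 80% power, 8 df (SD) |
|---|---|---|---|---|---|
| CCM | 45 | 0.60 | 80% | 70.4% | 3.20 × √(2/45) = 0.675 |
| Friends and family | 252 | 0.25 | 80% | 69.2% | 3.20 × √(2/252) = 0.285 |
| Residents, 400 per arm | 113.5 | 0.36 | 77% | 66.3% | 0.425 |
| Residents, 500 per arm | 124.3 | 0.36 | 81% | 70.1% | 0.406 |

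On the article's conversion of 0.60 SD to about 1 unit, 0.675 SD is 0.675/0.60 ≈ 1.1 LS7 units.

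**Step 3: the friends and family row is a best case.** The 252 treats each CCM as the cluster and leaves no separate community-level variance. The article gives no community-level ICC for this sample on its own. If, as an assumption, the whole 0.08 applied within communities, m = 358.4/5 = 71.7, the design effect is 6.65 and effective n is about 54. Power at 0.25 SD with 8 df would then be 21%, and 0.62 SD would be detectable. The range is therefore from 0.285 SD upward.

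**Step 4: the mixed-model test, if referred to a normal distribution.** The check was 400,000 simulated null trials with five equal clusters per arm and the REML community variance truncated at zero. They gave a two-sided type I error of 5.6% for CCM and 7.8–8.1% for residents. The upper limit is P(|t₈| > 1.96) = 8.6%. The CCM excess is small because the community variance is estimated as zero in about 37% of trials.

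**The case against.** The strongest defence is that the 70% belongs to the sizing t-test, whereas the planned model adjusts for baseline. With 8 df and the ICC unchanged, CCM power at 0.60 SD would be 74% at a baseline-to-24-month correlation of 0.3, 78% at 0.4, 82% at 0.5 and 88% at 0.6. The 80% level is regained at about 0.46 for CCM, 0.48 for friends and family (on n = 252) and 0.46–0.53 for residents. So a reader should not infer that the planned analysis must be underpowered. But the article neither gives such a correlation nor takes credit for one, and adjustment for each person's baseline adds no between-community df. The printed effects are not rescued by an unstated input.

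A second defence concerns error rates. A reader might infer that the primary test will exceed 5%. The document does not support that. It specifies a random community effect and is silent on df, a detail commonly left to a statistical analysis plan, and that plan is not shown here.

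A third point concerns the pairing. A reader might go further and use 4 df because the communities are paired, which would put power at about 54–58%. The stated model has no pair term, and those figures omit any gain from matching. They are hypothetical.

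**Conclusion.** The power statement is wrong on the document's own inputs. The three effects are presented as detectable with 80% power. With the 8 df that ten communities allow, power is about 70% (CCM), 66–70% (residents) and at best 69% (friends and family), and the effects that do have 80% power are about 13–14% larger. For residents at 400 per arm the plan's own method already gives 77%, so the fall there is from 77% to 66%.

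This rests on equal cluster sizes, the stated ICCs and attrition, an unadjusted contrast and an analysis that ignores pairing. The friends and family figure also depends on accepting 252, which omits community-level clustering. The within-town ICCs quoted at the start of Methods run to 0.04; at that value residents would need about 0.47–0.49 SD with 8 df.

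The error-rate part is not a stated error. It supports a recommendation only.

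**What to change.** In Sample size determination, restate the effects detectable with 80% power on 8 df: about 0.67 SD for CCM (about 1.1 LS7 units), 0.41–0.42 SD for residents, and no smaller than 0.285 SD for friends and family, saying which unit the ICC of 0.08 refers to. Alternatively, state the baseline correlation relied on and show that 80% is reached with it on 8 df.

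As a recommendation, name a small-sample method for the arm effect in the mixed model (Kenward-Roger, Satterthwaite, or t on 8 df), in the article or in the statistical analysis plan if it is not already there.

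The cost is restated figures and one software option. Recruitment, conduct and the form of the model stay as they are.
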